## Abstract

**Background:**

Raynaud’s phenomenon is one of the first clinical manifestations observed in systemic sclerosis (SSc). This microvasculature disorder affects mostly the digits in over 95% of SSc patients, significantly affecting their health-related quality of life (HRQoL) and incurring higher hospital admissions and other healthcare costs. Exercise is known to improve both micro- and macrovascular function – aerobic exercise and resistance training, separately or combined, have been demonstrated to lead to significant vasculo-physiological improvements in conditions that present vasculopathy. However, the effects of a combined exercise programme on microcirculation in SSc patients has yet to be investigated. Therefore, the purpose of this study is to assess the effects of high-intensity interval training (HIIT) combined with circuit resistance training on the microvascular function in the digital area of SSc patients.

**Methods:**

This will be a randomised controlled, feasibility trial with two arms, wherein 30 patients with SSc in receipt of medical treatment will be randomly assigned to usual care (medical treatment) or to a 12-week supervised exercise programme. Patients in the exercise group will undertake two, 45-min sessions each week consisting of 30 min HIIT (30 s 100% peak power output/30 s passive recovery) on the arm crank ergometer and 15 min of upper body circuit resistance training. Patients will be assessed before as well as at 3 and 6 months following randomisation. Primary outcomes of the study will be recruitment and retention rate, intervention acceptability and adherence to the exercise programme. Secondary outcomes include the digital area cutaneous microvascular function (laser Doppler fluximetry combined with iontophoresis), physical fitness, functional ability, upper back transcutaneous oxygen tension, body composition and quality of life (EQ-5D-5L). Selected interviews with a subsample of patients will be undertaken to explore their experiences of having Raynaud’s phenomenon and the acceptability of the exercise intervention and study procedures.

**Discussion:**

Data from this study will be used to identify the feasibility of a combined exercise programme to be implemented in SSc patients, the acceptability of the intervention and the study design, and to determine the effects of exercise on the microvasculature. Overall, this study will provide sufficient data to inform and support a full multicentre clinical trial.

**Trial registration:**

ClinicalTrials.gov (NCT number): NCT03058887, February 23, 2017.

**Electronic supplementary material:**

The online version of this article (10.1186/s13063-018-2980-1) contains supplementary material, which is available to authorized users.

## Background

Systemic sclerosis (SSc) is an autoimmune connective tissue disease characterised by tissue fibrosis and vascular involvement. Vasculopathy is directly implicated in the pathogenesis of SSc representing acute manifestations (e.g. pulmonary arterial hypertension, digital ulcers). Raynaud’s phenomenon (RP) is one of the first clinical manifestations presented in SSc, with a 95% prevalence across patients. RP precedes any other clinical symptoms of SSc and is due to hypoxia in the extremities in response to cold. Evidence suggests that endothelial injuries in conjunction with an imbalance in the vascular tone trigger RP [1], which in turn develops digital ischemia, a serious complication for patients with SSc. Morbidity rates in patients with SSc due to digital ischemia reach approximately 30% annually [2]. Patients with chronic digital ulcers develop irreversible tissue loss [2], which usually requires hospitalisation for iloprost infusion [3] lasting from 5 days to 3 weeks. Hospitalisation is a psychologically stressful procedure for the patient, directly affecting their health-related quality of life (HRQoL). The most common side effects of iloprost infusion are headache, flushing of the skin, nausea, vomiting and sweating. Amputation has been reported to occur in one or more digits due to ischemia in 20.4% of patients with SSc, 9.2% of which have multiple digit loss [4].

A recent review paper has aggregated the studies that have examined the effects of exercise in SSc patients with and without pulmonary involvement [5], summarising the beneficial effects, including good exercise tolerance and increased aerobic capacity [6–8], muscle strength [6, 9], hand mobility, [10–12], functional ability in daily activities [11] and increased HRQoL [10, 11]. However, most studies lacked reporting of the intensity of their exercise programme and none examined the effects of exercise on the vasculature. Therefore, it is important to explore the feasibility of a training protocol that would be able to (1) improve vascular function and potentially decrease the frequency and severity of digital ischemia and ulcers, and (2) have the potential to decrease the use of pharmacological agents. These agents are used to improve microcirculation with short-term (e.g. oedema, headaches, heart palpitations, dizziness and constipation) and long-term (e.g. heart dysfunction, increased cardiovascular risk) side effects and financial cost implications.

High-intensity interval training (HIIT) has demonstrated its efficacy in improving the endothelial function in the macrovasculature compared to moderate intensity continuous training in a range of clinical conditions with impaired vascular function [12]. HIIT has been shown to improve cardiorespiratory fitness, cardiovascular risk factors and biomarkers associated with vascular function. A HIIT protocol with short intervals (30 s exercise/30 s passive recovery; no exercise during resting intervals) may elicit more favourable patient-reported satisfaction/enjoyment levels compared to other longer duration exercise protocols [13]. In chronic heart failure patients, a short duration HIIT protocol (30 s exercise/30 s passive recovery) was demonstrated to be well tolerated, a preferred protocol with a low perception of effort, greater patient comfort and with a longer time spent at higher percentage of peak oxygen uptake (VO_2peak_) than a longer duration HIIT protocol with active recovery phases (low intensity exercise during resting intervals) [13].

Resistance training (RT) alone has been demonstrated to be effective in improving the endothelial vascular function in obese [14] and type 2 diabetes mellitus patients [15] where a vascular dysfunction is present in the pathophysiology of these conditions. The intensity of the RT ranged from 75 to 85% of one repetition maximum for 8 to 12 weeks (twice or thrice per week). However, a combined exercise regime (aerobic and RT) has also shown significant improvements in endothelial vascular function in a range of clinical conditions. More specifically, Metsios et al. [16] examined the effects of a combined exercise protocol in rheumatoid arthritis patients who performed a 6-month exercise intervention. Endothelial function was assessed via laser Doppler fluximetry (LDF) imaging using iontophoresis. The results indicated that an individualised aerobic and strength training programme significantly improves both micro- and macrovascular endothelial function in patients with rheumatoid arthritis. Other studies that have implemented a combined exercise protocol in chronic heart failure [17] and type 2 diabetes mellitus patients [18] have demonstrated a significant improvement in the microvascular reactivity of the forearm conduit and resistance vessels after an 8-week programme. Consequently, it seems that either RT alone or a combined protocol are able to improve endothelial vascular function.

To our knowledge, the feasibility of a combined HIIT protocol with short intervals (30 s at 100% peak power output and 30 s passive recovery) and a circuit RT programme on SSc patients has not yet been examined. Moreover, the efficacy of exercise on microcirculation in SSc patients constitutes another unexplored element of SS. Therefore, the primary aim of our study would be to investigate the feasibility of exercise in patients with SSc and the secondary aim is to explore the effects of exercise on microcirculation. Our study objectives are (1) to estimate the rates of recruitment and retention for a future definitive trial of a 12-week supervised exercise programme for SSc patients; (2) to estimate the rates of attendance to and compliance with the supervised exercise programme; (3) to assess the tolerance, acceptability and enjoyment levels of the training protocol; (4) to investigate the effects of exercise on microvascular reactivity in the digital area; (5) to identify and quantify the training dose that may induce microcirculatory improvements in SSc patients; (6) to assess the effects of exercise on HRQoL of SSc patients measured through generic questionnaires and interviews; and (7) to conduct post-intervention interviews with patients to explore individual’s experiences of the study’s procedures and exercise programme.

## Methods/Design

### Study design

The FESS (Feasibility of Exercise in Systemic Sclerosis patients) study is a mixed methods feasibility study involving a randomised controlled trial. Thirty patients with SSc receiving usual care (e.g. medical treatment) will be randomly assigned (via block randomisation remotely by the study chief investigator) to either an exercise group (12-week supervised exercise programme) or to a control group being in receipt only of the usual care. Patients will be followed for 6 months following randomisation (Fig. 1). It is not feasible to perform masking of patients or study investigators regarding the allocated treatments due to limited resources. The study is being run at Sheffield Hallam University in collaboration with the Royal Hallamshire Hospital (Sheffield Teaching Hospitals, NHS, UK). The study’s protocol and registration have been published in ClinicalTrials.gov (NCT number: NCT03058887).

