### Data management

The study will adhere to the Data Protection Act (1998). Data from this study will be anonymised and stored in password-protected computer systems accessible only by the members of the research team in order to guarantee confidentiality to patients. Paper forms will be stored in locked filing cabinets. All data documents will be kept in a secured and continuously monitored building where the project will be conducted ([name], Sheffield Hallam University). All study materials will remain in this location for data entry and storage. Double data entry will be implemented to ensure validity and data quality. Participant names will not be used to identify any data. Instead, patients will be assigned a study identification number in order to anonymise their information.

Data will all be anonymised according to the NHS Code of Confidentiality and GMC Good Medical Practice, while publications will not contain identifiable personal data. Furthermore, only research team members will have access to personal patient data during the project, while data will be analysed locally by the study’s statistician. Data will be kept for a 10-year period following the study completion to allow the study team to re-analyse it in case of the development of a new method of analysis and for the data to be used for the development of a future definitive RCT.

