### Secondary outcomes

#### Digital cutaneous microvascular function

##### Iontophoresis

Microvascular assessments using LDF and iontophoresis (as described in the literature; [22]) will be performed in a temperature-controlled room (22–24 °C). LDF electrodes will be attached to the dorsal aspect of the reference fingers for acetylcholine (ACh) and sodium nitroprusside (SNP) administration. These will be used as indicators of the changes occurring in the endothelial (dependent and independent) vasodilatory function. HR (Sports Tester, Polar, Finland) and blood pressure of the brachial artery (left arm; Dinamap Dash 2500, GE Healthcare, USA) will be monitored at 5-min intervals throughout the protocol. The two drug delivery electrodes (PF383; Perimed AB, Jarfalla, Sweden) will be positioned over the healthy-looking skin, approximately 4 cm apart with one containing 100 μL of 1% ACh (Miochol-E, Novartis, Stein) and the other 80 μL of 1% SNP (Nitroprussiat, Rottapharm). A battery-powered iontophoresis controller (PeriIont PF382b; Perimed AB) will be used to provide the charge needed for ACh and SNP delivery. A 4 min stable recording of baseline flux will be followed by administration of the two agents according to the following protocol: 0.2 mA for 10 s (i.e. 2 mC), 0.2 mA for 15 s (i.e. 3 mC), 0.2 mA for 20 s (i.e. 4 mC), and 0.3 mA for 20 s (i.e. 6 mC), occurring between 4-min intervals [21, 22]. To obtain an index of skin blood flow, cutaneous red cell flux will be measured by placing an iontophoresis laser Doppler probe (PF481–1; Perimed AB), connected to a laser Doppler fluximeter (PF5001; Perimed AB).

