### Statistical analysis

The sample size for a feasibility study should be adequate to estimate the critical metrics needed to assess the feasibility of conducting the definitive study, with sufficient precision [34]. The critical metrics are the consent rate (i.e. the proportion of eligible patients who consent to participate and be randomised), improvement in microcirculation and quality of life as well as compliance with treatment, and attrition rates. Fifteen patients in each group (*n* = 30 in total) will provide a sufficiently precise (within 15 percentage points for a 90% confidence interval) estimate of the proportion willing to be randomised, assuming 35–40% intention to be randomised.

The SPSS software (version 23, IBM SPSS, New York, USA) will be used to enter quantitative data and cleaning the data and to carry out missing values imputation and statistical analysis. The descriptive statistics, including mean and standard deviation, will be presented for basic demographics and primary and secondary outcomes of the patients in intervention and control groups. For categorical data, the χ^2^ test will be used to infer on the significant association. Independent and paired samples *t* tests will be used to account for the changes upon the primary and secondary outcomes within the group at pre- and post-exercise intervention but also between the two groups. Kolmogorov–Smirnov and Shapiro–Wilk tests will be used to test the normal distribution of the dependent variable and Levene’s test will be used to test the homogeneity of variances. Pearson’s r will test any relations and interactions between our variables. The qualitative analysis will be performed using framework analysis [35], aiming to describe individuals’ experiences of exercise, searching for common, recurrent patterns but also exploring participant experiences that might explain behaviour and improve advice and services in the future. Data saturation will be achieved when similar themes arise repeatedly and no new themes arise in the interview.

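### Masking is declined for patients and investigators on one blanket reason, and no masked reading of the laser Doppler flux data is planned

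*Protocol article*

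**What the plan says.** The Study design section of the protocol article deals with masking in one sentence: "It is not feasible to perform masking of patients or study investigators regarding the allocated treatments due to limited resources". The same section has the allocation done "via block randomisation remotely by the study chief investigator".

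The microvascular outcome is described under Iontophoresis. The procedure begins as follows: "A 4 min stable recording of baseline flux will be followed by administration of the two agents". Four charges are then given (2, 3, 4 and 6 mC), for acetylcholine (ACh) and for sodium nitroprusside (SNP), and "cutaneous red cell flux will be measured by placing an iontophoresis laser Doppler probe". The article does not say who derives the baseline and response values from this signal.

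The abstract lists digital microvascular function as a secondary outcome; the primary outcomes concern feasibility. The Statistical analysis section nevertheless names among the critical metrics "improvement in microcirculation and quality of life as well as compliance with treatment, and attrition rates", and plans t tests between the two groups on the primary and secondary outcomes.

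Under Data management, "patients will be assigned a study identification number in order to anonymise their information". The same section provides for double data entry and for analysis by the study's statistician, and adds: "All study materials will remain in this location for data entry and storage".

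**The concern.** One reason is made to serve several separate decisions. Patients cannot be masked to supervised exercise whatever the budget, and neither can the staff who run the sessions. Whether the person reading flux values from a recording knows the arm is a different question. The masking sentence does not address it, and nothing elsewhere in the article does.

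Deriving flux may call for judgement: which stretch of the signal counts as stable baseline, and which part represents the response after each charge. If these choices are made with the arm and visit in view, a preference for the expected result can enter the between-group comparison. No later analysis can remove it. At stake is the credibility of an exploratory comparison that the Discussion section expects to inform a definitive multicentre trial.

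**Working it through.** The plan states no figure on masking, so the main check sets its statements side by side.

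**1. Who is covered.** The masking sentence names patients and study investigators. It does not mention a separate reader of recordings or the statistician. Masked reading is therefore neither planned nor expressly excluded.

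**2. Whether something else already protects the reading.**
- Study identification numbers replace names for confidentiality. They do not hide arm or visit.
- Double data entry catches keying errors. It does not check how a value was taken from a trace.
- Remote allocation concerns the assignment, not the later assessment, and the chief investigator who performs it knows the arms.

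**3. Whether coded reading is plausible.** The Iontophoresis section speaks of a recording, and Data management describes on-site storage and a statistician. That traces are saved as files is a fair inference, but it is not stated.

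**4. Workload.** There are 30 patients and three assessments (baseline, 3 and 6 months).
- Sessions: 30 x 3 = 90.
- Traces, if ACh and SNP are filed separately: 90 x 2 = 180.
- Sessions recorded after randomisation: 30 x 2 = 60. The abstract places the first assessment before randomisation, so knowledge of the arm can affect acquisition only in these 60. Reading can be affected in any trace that is read after allocation.

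Both totals are upper limits, since dropouts reduce them.

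**5. Illustration under assumption.** The documents give neither an SD for flux nor a size for reader bias. Suppose there is no true effect and unmasked reading shifts the between-arm difference by b SD. For a two-sided 5% two-sample t test with 15 per arm (28 df), the noncentrality is b / sqrt(2/15) = b / 0.365. The rejection rates are:

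| Assumed shift b (SD) | Rejection rate |
|---|---|
| 0 | 5.0% |
| 0.1 | 5.8% |
| 0.2 | 8.3% |
| 0.3 | 12.5% |
| 0.5 | 26.2% |

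For comparison, the 90% confidence interval for the between-arm difference has half-width t(28, 0.95) x sqrt(2/15) = 0.62 SD. Unless the shift is large, sampling error dominates. Coded reading would remove only the part of a shift that arises in reading.

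**6. Effect of the change on sample size.** None. The stated precision for the proportion willing to be randomised, taken with 30 as the denominator, is 1.645 x sqrt(0.35 x 0.65 / 30) = 14.3 points, and 14.7 points at 40%. Both lie within the stated 15 points and do not depend on masking.

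**The case against.** The strongest reply is that this is an article, not the full protocol. It refers to published descriptions of the iontophoresis method, and details of extraction commonly sit in a laboratory procedure or analysis plan that is not shown. That stands: the lack of an extraction rule is not an error here. What remains open to comment is the masking decision itself, which the article does state, with one reason that fits its several parts poorly.

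The second reply is that flux is an instrument output, taken after fixed charges at 4-minute intervals in a temperature-controlled room. A trace reader may have little discretion, and the larger risk may lie in choosing the skin site and placing the probe, which coding cannot touch. That also stands, and it limits what the change can achieve.

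A reader of the protocol might infer more than the text supports in three ways:
- **That all masking is ruled out.** The sentence covers patients and study investigators only.
- **That unmasked staff will read stored traces by judgement.** The article states neither the storage of traces, nor who reads them, nor how much discretion is involved.
- **That 15 patients per arm makes the problem worse.** A systematic shift cannot be told apart from an effect at any sample size, and it matters relatively less when sampling error is large.

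**Conclusion.** The point holds as a modest improvement to the design. Masking is declined for patients and investigators on a single reason, no masked reading of flux is planned, and whoever derives the values may know the arm. The article itself counts improvement in microcirculation among its critical metrics, which is why the point is worth making for a secondary outcome.

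The size of any reader bias is unknown. The rejection rates above show only how an assumed shift would act; they are not evidence that one exists. A reader might infer that the flux comparison will be biased by some definite amount, but the documents contain nothing from which to estimate it, and it may be small.

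Recruitment, retention, acceptability and adherence are untouched. The proposal assumes that flux traces are saved and can be read later. If they are not, the article need only say so.

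**What to change.** Amend the masking sentence under Study design to separate the roles:

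- Patients, exercise staff and recording sessions are unmasked. The reason for each is given.
- Where flux traces are saved, the study statistician re-labels each file with a random code that hides arm, visit and date.
- An existing team member extracts baseline and response values from the coded files by a rule fixed in advance.
- The extracted values are locked before the arm code is merged.

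If coded reading cannot be done, say why.

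No extra reader is needed, because the code hides the arm from existing staff. The cost is re-labelling up to 90 sessions (or up to 180 traces), with extraction waiting until the files are coded. Sample size and patient procedures do not change. The masking is partial: bias from skin site, probe placement and conduct of the session remains, and someone who took a recording might still recognise it. The article should state this limit.

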**Fig. 1 Fig1:**
[figure not shown]
Study design

This study started in February 2017 and is due to be completed by May 2018. The trial is sponsored by the Vice Chancellor’s Fellowship award of Sheffield Hallam University, and ethical approval was granted by the NHS Health Research Authority, London Committee (16/LO/0811), which allows ethical permission across Sheffield Hallam University and Royal Hallamshire Hospital (Sheffield Teaching Hospitals).

### Recruitment of participants

Patients conforming to the eligibility criteria will be recruited from the Rheumatology Department of the Royal Hallamshire Hospital in Sheffield or will be self-referred by seeing a poster in this location, through responding to a public announcement, or after being notified of the study via word of mouth. Patients recruited via hospital clinics will be invited for participation through an invitation letter (including the contact details of a research team member) accompanied by a patient information sheet. Patients who express an interest (calling or posting back) will be contacted by the research team to confirm their eligibility, addressing any inquiries regarding the study and arranging the first visit. Clinical care will not be affected for those not wishing to take part in the study nor those who decide to withdraw from the study.

The first visit will take place at the Centre for Sports and Exercise Science at Sheffield Hallam University laboratories, where the patient will be given further details of the study procedures and will be asked to sign a consent form to participate in the research study. Afterwards, patients will be habituated with the trial processes and will complete the baseline assessments.

